## Abstract

**Background:**

Postoperative pulmonary and shoulder complications are important causes of postoperative morbidity following thoracotomy. While physiotherapy aims to prevent or minimise these complications, currently there are no randomised controlled trials to support or refute effectiveness of physiotherapy in this setting.

**Methods/Design:**

This single blind randomised controlled trial aims to recruit 184 patients following lung resection via open thoracotomy. All subjects will receive a preoperative physiotherapy information booklet and following surgery will be randomly allocated to a Treatment Group receiving postoperative physiotherapy or a Control Group receiving standard care nursing and medical interventions but no physiotherapy. The Treatment Group will receive a standardised daily physiotherapy programme to prevent respiratory and musculoskeletal complications. On discharge Treatment Group subjects will receive an exercise programme and exercise diary to complete. The primary outcome measure is the incidence of postoperative pulmonary complications, which will be determined on a daily basis whilst the patient is in hospital by a blinded assessor. Secondary outcome measures are the length of postoperative hospital stay, severity of pain, shoulder function as measured by the self-reported shoulder pain and disability index, and quality of life measured by the Medical Outcomes Study Short Form 36 v2 New Zealand standard version. Pain, shoulder function and quality of life will be measured at baseline, on discharge from hospital, one month and three months postoperatively. Additionally a subgroup of subjects will have measurement of shoulder range of movement and muscle strength by a blinded assessor.

**Discussion:**

Results from this study will contribute to the increasing volume of evidence regarding the effectiveness of physiotherapy following major surgery and will guide physiotherapists in their interventions for patients following thoracotomy.

**Trial registration:**

The study protocol is registered with the Australian and New Zealand Clinical Trials registry (ANZCTRN12605000201673).

## Background

Physiotherapy interventions have been regularly utilised in the prevention and treatment of both pulmonary and musculoskeletal complications following major surgery since the 1960s. Following thoracotomy, postoperative pulmonary complications (PPCs) are an important cause of morbidity, contributing to significant increases in health care costs, length of intensive care and hospital stay and patient discomfort [1-5]. In some major surgical patient groups there has been a steadily accumulating body of evidence demonstrating that postoperative *prophylactic *physiotherapy for the prevention of PPCs and musculoskeletal problems may be unnecessary [6-12]. Whilst physiotherapy for thoracic surgical patients continues to be strongly advocated, to date there have been no randomised controlled trials supporting its effectiveness. Evidence from a recent cross sectional study with historical controls in patients following lung resection suggests that physiotherapy may reduce length of hospital stay and incidence of atelectasis (with a subsequent reduction in hospital costs) but appears to have no influence over the incidence of pneumonia and overall morbidity [13]. Other research has demonstrated that adding various adjuncts (such as incentive spirometry) to usual care physiotherapy treatment programmes makes no significant difference to outcome, however to date there have been no randomised controlled trials including a no treatment group [14-17]. It remains unknown whether prophylactic respiratory physiotherapy, as part of inpatient postoperative recovery, is necessary following pulmonary resection and clarification of the role and efficacy of these interventions is overdue.

Thoracotomy may also lead to chronic pain and long term restriction of shoulder function and physiotherapy and early mobilisation are commonly recommended and implemented to prevent these problems [18,19]. Whilst shoulder range of movement, strength and function has been extensively examined in this patient group [20-24] the role of a postoperative physiotherapy exercise programme in minimising this dysfunction has not been investigated. Significant correlation between upper limb morbidity and poorer quality of life has been reported in patients in other surgical groups [25]. A study to evaluate the effectiveness of a shoulder and thoracic cage exercise programme following thoracotomy should further develop an understanding of both short and long term shoulder morbidity in this patient group.

The Physiotherapy Management of the patient undergoing Thoracic Surgery study (PMoTS) was designed as there are no published RCTs which address these outcomes.

### Aims and Hypotheses

Thus the primary aims of the study are to:

1. Compare the incidence of PPCs between groups

2. Compare the postoperative length of hospital stay (LOS) between groups

The secondary aims are to:

3. Compare LOS in those subjects who develop PPCs and those who do not.

4. Compare the recovery of shoulder function, shoulder range of motion (ROM), and shoulder muscle strength (MMS) between groups

5. Compare the health related quality of life (HRQoL) between groups

The study hypothesis for the primary aims is:

H1. Routine postoperative prophylactic physiotherapy will significantly reduce the incidence of PPCs and LOS compared to no postoperative physiotherapy following open thoracotomy.

The hypothesis for the secondary aim is:

H2. A postoperative exercise programme will significantly improve the recovery of shoulder ROM, muscle strength and function following open thoracotomy.

## Methods and Design

### Study design

The PMoTS study is a single blinded randomised controlled trial of patients undergoing elective pulmonary resection via open thoracotomy in one thoracic surgical unit in New Zealand. The study aims to investigate the effectiveness of physiotherapy treatments following surgical removal of part or whole of one lung.

### Subjects

#### Inclusion/exclusion criteria

To be eligible for enrolment subjects must be adults admitted to Auckland City Hospital, New Zealand to undergo elective lung resection via open thoracotomy. They must understand written and spoken English and give informed written consent. Subjects will be excluded if they are unable or unwilling to comply with treatment, have tumour invasion into the chest wall or brachial plexus, present with a PPC prior to randomisation on postoperative day one, remain ventilated for longer than 24 hours following surgery or have received physiotherapy for shoulder problems or respiratory problems within two weeks prior to admission for surgery. Subjects with postoperative neurological or mobility complications requiring comprehensive physiotherapy input to progress towards discharge (defined as being more than two physiotherapy interventions), will be provided with the physiotherapy as required, remain in the group to which they were allocated and analysed using intention to treat principles. Subjects, who live within a 60 km radius of Auckland Hospital and can attend outpatient appointments, will form a subgroup that, in addition to all other measures, will attend for follow up shoulder ROM and muscle strength measures.

#### Sample size

Sample size was calculated for the primary outcome measure of PPC with a type I error rate of .05 and a type II error rate of 0.20 (80% power). Estimates of the incidence of PPCs vary throughout the literature dependent upon criteria used for diagnosis but best estimates suggest a PPC rate (after thoracotomy and amenable to physiotherapy interventions) of between 10–25% occurs in this population with routine physiotherapy care [4,14], Assuming a PPC rate of 20% in the Control Group and 5% in the Treatment Group (thus a 15% difference in PPCs), 84 subjects in each group are required. Allowing for an estimated loss to follow up rate of 9% (based on similar studies) a sample size of 184 subjects (92 per group) is necessary to demonstrate sufficient power for the primary outcome. Because there are no randomised trials that include a control group on which to accurately base this sample size calculation, an interim analysis will be undertaken when total n = 80.

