#### b. Postoperative treatment

Both Treatment and Control Group subjects will receive standard nursing and medical care according to the clinical pathway in use at the unit where the research is being undertaken.

Subjects in the Treatment Group will receive postoperative physiotherapy from the attending ward physiotherapist as per a written protocol on a daily basis until discharge. This includes a *minimum *predetermined amount of: deep breathing and coughing exercises, assistance with ambulation, and a progressive shoulder and thoracic cage mobility exercise programme (see Figure 2). Subjects will be encouraged by the attending physiotherapist to practice the exercises outside physiotherapy treatment times but this practice will not be quantitatively measured. Upon discharge from hospital Treatment Group subjects will receive a discharge exercise and advice sheet with an exercise diary explained by the attending ward physiotherapist.

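### The 80% power claim holds only for 20% v 5%, and the 5% physiotherapy rate is half the lowest rate the protocol cites for physiotherapy patients

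*Protocol article*

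**What the plan says.** The Sample size section sets "a type I error rate of .05 and a type II error rate of 0.20 (80% power") for the primary outcome, the incidence of postoperative pulmonary complications (PPC). As its evidence it states that "a PPC rate (after thoracotomy and amenable to physiotherapy interventions) of between 10–25% occurs in this population with routine physiotherapy care", and attaches two references. The planning values follow: "Assuming a PPC rate of 20% in the Control Group and 5% in the Treatment Group (thus a 15% difference in PPCs"). These lead to 84 per group, raised to 92 per group (184 in total) for 9% loss.

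The Postoperative treatment section fixes which arm is which: "Subjects in the Treatment Group will receive postoperative physiotherapy from the attending ward physiotherapist as per a written protocol on a daily basis until discharge". Control subjects receive no postoperative physiotherapy.

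The Sample size section also concedes that no randomised trial with an untreated control group was available as a basis, and for that reason plans an interim analysis at a total of 80. The Data analysis section names a chi-squared test for PPC and says that the absolute risk reduction and number needed to treat will be calculated.

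**The concern.** The cited range describes patients who had routine physiotherapy, so its natural counterpart in this trial is the Treatment Group. The calculation instead gives a value from that range to the arm without physiotherapy. It then gives the physiotherapy arm 5%, half the lower end of the range, with no source. The implied relative reduction is (20 − 5)/20 = 75%.

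The only comparative evidence on physiotherapy v none that the Background cites for lung resection is a cross-sectional study with historical controls. It suggests a possible reduction in atelectasis and in length of stay, but physiotherapy there "appears to have no influence over the incidence of pneumonia and overall morbidity". That is mixed evidence, and it does not supply a basis for a 75% reduction in a composite that needs four of eight criteria.

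What is at stake is how a null result will be read. The trial asks whether routine physiotherapy is needed at all. An unconditional statement of 80% power lends a non-significant result more weight than it may deserve.

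**Working it through.** **Inputs.** Two-sided alpha 0.05 (sidedness is not stated; two-sided is assumed because the planned test is chi-squared), power 80%, equal allocation, rates 20% and 5%, 84 per group before loss and 92 after: Sample size section. Test: Data analysis section. Range of 10–25% under physiotherapy: Sample size section.

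**Step 1: reproduce the 84.** With mean rate p̄ = 0.125:

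n = [1.96·√(2p̄(1−p̄)) + 0.842·√(p₁(1−p₁) + p₂(1−p₂))]² / (p₁−p₂)²

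= [1.96·√0.21875 + 0.842·√0.2075]² / 0.0225 = (0.917 + 0.383)² / 0.0225 ≈ 75.1, so 76 per group.

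With a continuity correction, (n/4)·[1 + √(1 + 4/(n·0.15))]², this becomes 88. The unpooled-variance version with the same correction gives 85.2, and the arcsine version gives 82.0. Exact power at 84 per group for 20% v 5% is 79.6% with the Yates correction, 81.7% with Fisher's test and 86.7% with the uncorrected chi-squared test. The stated 84 is therefore a reasonable figure for 80% power at 20% v 5%.

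**Step 2: move the Treatment rate into the cited range.** Exact power sums the two binomial distributions over all tables in which the uncorrected chi-squared statistic exceeds 3.84.

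| Control v Treatment | 84 per group | 92 per group |
|---|---|---|
| 20% v 5% (as planned) | 87% | 90% |
| 25% v 10% | 74% | 78% |
| 30% v 15% | 66% | 69% |
| 35% v 20% | 59% | 63% |
| 40% v 25% | 55% | 59% |
| 20% v 10% | 44% | 48% |
| 20% v 15% | 14% | 14% |

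Rows 2 to 5 keep the protocol's 15-point difference. The last two keep its 20% Control rate; with Treatment at 20% or above there is no benefit left to detect. No row with a Treatment rate in the cited range reaches 80%, even with nobody lost. A continuity correction lowers the figures further: 25% v 10% at 84 per group gives 67%.

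**Step 3: what would restore 80%.** Solving the normal-approximation power formula at 84 per group for the Control rate:

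| Treatment | Control needed | Difference |
|---|---|---|
| 10% | about 27% | 17 points |
| 15% | about 33% | 18 points |
| 20% | about 40% | 20 points |
| 25% | about 46% | 21 points |

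**Step 4: cost of keeping 15 points at 80% power.** The uncorrected formula of Step 1 gives 100 per group for 25% v 10%, 121 for 30% v 15%, 138 for 35% v 20% and 152 for 40% v 25%, all before loss.

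**The case against.** Five points can fairly be made for the plan.

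- **The true no-physiotherapy rate is unknown.** If physiotherapy works and treated patients run at 10–25%, untreated patients should run higher, perhaps high enough. Exact power at 84 per group is 83% for 27% v 10% and 82% for 40% v 20%. This stands. A reader might infer that the trial is underpowered as a matter of fact; the article does not support that, because it gives no untreated rate other than 20%.
- **The cited range may not transfer.** The article says that published rates depend on the diagnostic criteria. This trial requires four of eight criteria and excludes patients with a PPC before randomisation on day one and those ventilated beyond 24 hours. A rate below 10% is therefore conceivable. This stands as a possible justification, but the article does not offer it for the 5%, and it would tend to lower both arms.
- **The Background is not wholly negative.** It would be too strong to say that it contradicts any effect on PPC: it reports a possible reduction in atelectasis, which is part of the first PPC criterion.
- **Loss may hardly touch the primary outcome.** PPC is recorded in hospital and analysed by intention to treat, so the analysed number may approach 92 per group. At the low end of the range the shortfall is then about 2 points (78%). It widens to about 21 points at the high end (59%).
- **The uncertainty is disclosed.** This is so, but the admission concerns the absence of an untreated comparison. It does not explain why the physiotherapy arm, for which evidence is cited, departs from that evidence. The article ties no re-estimation rule to the look at 80.

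**Conclusion.** The concern holds in conditional form. The sample size is arithmetically sound for 20% v 5%, but the 5% is unsourced and lies outside the range that the same paragraph gives for patients receiving physiotherapy. The 80% therefore holds only under that assumption. If the Treatment rate is anywhere in 10–25%, power is 55–74% at 84 per group (59–78% at 92) for the planned 15-point difference, and at most 44% (48%) with Control at 20%.

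These figures assume a two-sided 5% uncorrected chi-squared test and equal arms. They also assume that either the protocol's difference or its Control rate is kept. They do not show that the trial must fail to reach 80%, since an untreated rate 17 to 21 points above the Treatment rate would restore it. The article neither states nor supports such a rate.

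**What to change.** Keep N at 184 and rewrite the Sample size paragraph.

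1. Align the Treatment rate with the cited 10–25%, or give the basis for 5%, for example the four-of-eight definition and the exclusion of early PPCs. State the assumed no-physiotherapy rate with its basis.
2. Replace the single power claim with one that is explicitly conditional on 20% v 5%. Add the power for Treatment rates of 10%, 15%, 20% and 25% and the differences detectable at 80% (about 17, 18, 20 and 21 points).
3. State that a non-significant result will be interpreted from the 95% confidence interval of the absolute risk reduction.
4. If the look at n = 80 is used to update these figures, use the pooled PPC rate without unblinding. The article does not say whether that look is blinded. The planning values imply a pooled rate of (20 + 5)/2 = 12.5%, with a standard error at 80 subjects of √(0.125 × 0.875/80) ≈ 3.7 points, so it can flag only a large departure.

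The cost is one reworded paragraph and a less favourable stated power; no extra patients are needed. This makes the claim honest but restores no power. A sponsor who wants 80% for 15 points across the cited range would need the 100 to 152 per group shown in the working, before loss.

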### Ethics and study registration

Ethical permission for the study was granted from Northern X Regional Ethics Committee in October 2005. The study protocol is registered with the Australian and New Zealand clinical trials registry (ANZCTRN12605000201673). The flow of subjects through the study follows the CONSORT (Consolidated Standards of Reporting Trials) recommendations (see Figure 1).

**Figure 1 F1:**
[figure not shown]
Trial protocol.

### Procedures

#### Recruitment and randomisation

Subjects eligible to take part are screened from the thoracic surgical operating list by the study investigators (JR & KN) on admission to hospital. If eligible to take part the study investigators approach the subject to explain the study and gain informed consent. It is explained that they may withdraw from the study at any time without jeopardising their future care. On day one postoperatively, prior to any physiotherapy interventions and following extubation, subjects are given a consecutive study number and randomly allocated to the Treatment Group or Control Group by an independent physiotherapist. The ward physiotherapist is then told of the group allocation which is recorded and the envelope stored. Group allocation is assigned using a computer generated random allocation (from ) and individual group assignment is kept in sealed opaque envelopes.

In the event of more than one thoracic surgical procedure per day randomisation is performed according to order of admission onto the postoperative intensive care/surgical ward. To avoid influencing postoperative regimens, subjects taking part in the research trial are, where possible, allocated to separate rooms during their hospital stay.

In the subgroup who meet the inclusion criteria for shoulder ROM and muscle testing, a computer generated randomised order for performing the ROM and muscle strength measures is determined before preoperative measures and adhered to throughout the study. The randomisation order is generated from .

### Interventions

#### a. Preoperative education

After consent all subjects have preoperative demographic data recorded in order to compare baseline measures between groups (see Table 1), and are given a physiotherapy written information sheet by a study investigator. This broadly explains the need for postoperative breathing and coughing exercises, early ambulation, and shoulder mobility exercises. It outlines breathing exercises, huffing/coughing and the importance and progression of ambulation postoperatively. It gives general advice about shoulder and arm use in the postoperative period. No other form of preoperative physiotherapy education and treatment is provided to subjects in either group.

**Table 1 T1:** Demographic Data

▪ Age
▪ Ethnicity
▪ Sex
▪ Smoking history & pack year history
▪ Body mass index (BMI)
▪ American Society of Anaesthesiologists score (ASA)
▪ Hand dominance
▪ History and symptoms of chronic lung disease
▪ Relevant past medical history
▪ Percutaneous oxygen saturation (SpO_2_)
▪ Pulmonary function tests
◦ Forced Expiratory Volume in 1 second (FEV1)
◦ Forced Vital Capacity (FVC)
◦ FEV1/FVC
▪ Date of surgery
▪ Surgeon
▪ Surgical procedure
▪ Duration of anaesthesia
▪ Incision site/type of thoracotomy (muscle sparing, postero-lateral, antero-lateral, axillary)
▪ Rib resections
▪ Number of chest drains in situ, length of time on suction (number of days) and length of time in situ (number of days) postoperatively
▪ Postoperative analgesia and method of administration
▪ Relevant past medical history of shoulder or upper back/neck problems and management
▪ Presence of seroma at wound site (Y/N)
▪ Time to first sit out of bed (number of hours postoperatively)
▪ Time to first mobilisation > 10 metres or equivalent walk on spot if chest drains remain on suction (number of days postoperatively)
▪ Reason for increased length of stay
▪ Physiotherapy interventions administered (total number of sessions, cumulative time and type of intervention)
▪ Return to the intensive care unit and operating theatre
▪ Postoperative chemotherapy or radiotherapy

#### b. Postoperative treatment

Both Treatment and Control Group subjects will receive standard nursing and medical care according to the clinical pathway in use at the unit where the research is being undertaken.

Subjects in the Treatment Group will receive postoperative physiotherapy from the attending ward physiotherapist as per a written protocol on a daily basis until discharge. This includes a *minimum *predetermined amount of: deep breathing and coughing exercises, assistance with ambulation, and a progressive shoulder and thoracic cage mobility exercise programme (see Figure 2). Subjects will be encouraged by the attending physiotherapist to practice the exercises outside physiotherapy treatment times but this practice will not be quantitatively measured. Upon discharge from hospital Treatment Group subjects will receive a discharge exercise and advice sheet with an exercise diary explained by the attending ward physiotherapist.

**Figure 2 F2:**
[figure not shown]
Example of minimum physiotherapy intervention programme.

Control Group subjects will receive no postoperative physiotherapy. They may be verbally encouraged by attending nursing staff to practice the exercises outlined on their preoperative physiotherapy information sheet throughout their postoperative stay.

### Outcome measurement

Outcome measures, instruments used and timeframes for measurement are summarised in Table 2.

**Table 2 T2:** Summary of outcome measurements

**Primary Outcomes**	**Measurement instrument**	**Time point**
PPC	8 point item score (see Table 3)	Postop daily to discharge

**Secondary Outcomes**	**Measurement instrument**	**Time point**

LOS	Retrospective from patient information database	At discharge
SPADI	13 items scored on 11 point Likert scale	Preop, at discharge, 1 month postop, 3 months postop
ROM of shoulder flexion, elevation through abduction and external rotation (subgroup)	Plurimeter – V inclinometer	Preop, at discharge, 1 month postop, 3 months postop
MMS of shoulder abduction, flexion and internal rotation (subgroup)	Hand held dynamometer (Lafayette Instruments)	Preop, 1 month postop, 3 months postop
HRQoL	Short Form 36 v2 (NZ)	Preoperative, 1 month postop, 3 months postop
Pain	Body charts and verbal rating scale (end descriptors 0 = no pain and 10 = worst pain possible)	Preop, at discharge, 1 month postop, 3 months postop

Key : HRQoL – Health related quality of life, LOS – length of postoperative hospital stay, MMS – muscle strength, NZ – New Zealand, Postop – postoperative, PPC – postoperative pulmonary complication, Preop – preoperative, ROM – range of movement, SPADI – shoulder pain and disability index.

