#### 3. Shoulder function

Will be measured using the Shoulder Pain and Disability Index (SPADI) preoperatively, on discharge from hospital, one month and three months postoperatively. This is a self reported shoulder specific index developed by Roach et al. (1991) [26] which consists of 13 items in two subscales: pain (5 items) and disability (8 items). Each item is measured on an 11 point Likert scale where 0 = "no pain/no difficulty" and 11 = "worst imaginable pain/so difficult it required help" on each subscale respectively. The SPADI is scored by adding then averaging the two subscales to determine a score out of 100. A higher score means greater pain/disability. The SPADI has been demonstrated to detect change in subject's status over time, have good test-retest reliability, internal consistency and good criterion and construct validity although not within the thoracic surgical population [26-28].

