#### 4. Shoulder ROM

In a subgroup of patients living within a 60 km radius of Auckland Hospital, active ROM will be measured preoperatively, on discharge from hospital, one month and three months postoperatively by a blinded assessor using digital inclinometry via a Plurimeter-V inclinometer. ROM will be measured in those muscle groups which are divided during surgery thus potentially affecting range of movement. The measures are:

a. Total shoulder flexion (the movement includes scapular motion)

b. Total shoulder elevation through abduction (the movement includes scapular motion)

c. Glenohumeral external rotation

All ROM measures (except external rotation) are taken with the subject fully upright in a standardised chair with the opposite forearm resting on a fixed table to eliminate trunk movement. Sitting has been chosen as the starting position for most measures due to the possibility of subjects with respiratory disorders being unable to tolerate supine lying. The position of the inclinometer is established by measurement from a clear surface marking (e.g. 1 cm above lateral epicondyle).

▪ Shoulder flexion is measured with the arm at the side, elbow extended, shoulder in neutral rotation with palm facing the thigh and thumb facing forwards. The subject actively flexes the arm with the thumb leading throughout, maintaining elbow extension.

▪ Shoulder elevation is measured with the arm at the side, elbow extended, arm in external rotation with the palm facing forward. The subject actively elevates the arm leading with the thumb maintaining elbow extension.

▪ Shoulder external rotation is measured in supine lying (on a standardised bed) with the arm at side, humerus supported by the bed, elbow flexed to 90°, forearm in the mid prone position, hand in fisted position, pointing towards the ceiling. The subject actively externally rotates the arm maintaining the elbow on the bed and leading with the dorsum of the hand.

For all movements care is taken to avoid trunk assisted movements. On each occasion the arm is returned to 0° and each movement is repeated twice after one practice measure. These measures, where possible, follow a standardised protocol that has been shown to have acceptable intra and interrater reliability for use within a randomised controlled trial [29]. As well as recording ROM subjects report maximum pain during each movement on a 0 – 10 verbal rating scale. The maximum reading for pain for each movement is recorded.

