### Data analysis

Analyses will be conducted using an intention to treat principle for all randomised subjects. Demographic data will be analysed using descriptive statistics, Chi squared and Independent t tests or parametric equivalents.

A Chi squared test will be used to determine if there is any significant difference in the incidence of PPC between groups. LOS will be tested for normality of data. If normally distributed an Independent t test will be used to calculate the differences in mean LOS between groups and in differences in LOS in those subjects who do and do not develop PPCs. Data will be presented as mean differences with 95% confidence intervals. If data are not normally distributed a non parametric Mann Whitney U test will be used. The absolute risk reduction and number needed to treat will also be calculated for the primary outcome of PPC. Further between group comparisons for repeated measures of interval data (such as shoulder ROM, shoulder muscle strength, ADL and HRQoL) will be made using repeat measures ANOVA. Significant results will be analysed using post hoc tests such as the Scheffe F test. The alpha level for all statistical analyses will be set at 0.05.

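### SPADI, pain and shoulder ROM are compared at discharge, whose timing is itself an outcome; if stay differs and recovery is still under way, that contrast mixes treatment effect with days since surgery

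*Protocol article*

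**What the plan says.** Table 2 (Outcome measurement) gives SPADI, shoulder ROM and pain the same four time points: "Preop, at discharge, 1 month postop, 3 months postop". The text agrees. Section 3, Shoulder function, has SPADI taken "preoperatively, on discharge from hospital, one month and three months postoperatively", and section 4, Shoulder ROM, states that "active ROM will be measured preoperatively, on discharge from hospital, one month and three months postoperatively". The abstract also lists discharge as an assessment for pain and shoulder function. No section fixes a postoperative day for it. Muscle strength has no discharge measurement.

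LOS is an outcome in its own right. Aims and Hypotheses includes the aim "Compare the postoperative length of hospital stay (LOS) between groups", and H1 reads: "Routine postoperative prophylactic physiotherapy will significantly reduce the incidence of PPCs and LOS compared to no postoperative physiotherapy following open thoracotomy". The same section makes recovery of shoulder function and ROM a between-group comparison.

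Data analysis assigns "Further between group comparisons for repeated measures of interval data" to repeated-measures ANOVA, with post hoc tests after significant results. Shoulder ROM is among its examples. It mentions no use of the actual number of days since surgery.

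**The concern.** Allocation takes place on postoperative day one, and discharge follows at a time that treatment may change. Under the trial's own hypothesis, Treatment Group patients leave sooner, so their first post-randomisation SPADI, pain and ROM values would be taken on an earlier postoperative day. An ANOVA organised by visit label treats discharge as one common time level in both arms.

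If patients are still improving around discharge, the arm that leaves sooner looks worse at that level even with no true effect on the shoulder. A favourable result on LOS would then count against physiotherapy on early pain and shoulder function, either hiding a benefit or suggesting harm. If physiotherapy lengthened the stay, the distortion would favour it.

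**Working it through.** **1. What the plan supplies.** There is no figure on this point to reproduce: the article gives no expected LOS difference in days, no early recovery curve and no SPADI standard deviation. It does give 84 per group, 20% versus 5% PPC, alpha 0.05 and 80% power. The two-sided Fisher test with 84 per group has exact power of 81.7% for those rates, so 84 is a reasonable working number. It serves below only as the number per arm.

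**2. Formula.** Let D be the difference in mean LOS (Control minus Treatment, in days) and s the daily fall in SPADI near discharge, taken as constant. A higher SPADI is worse. With no true shoulder effect, the expected Treatment minus Control difference at discharge is b = D × s. It is zero if D = 0, and also if s = 0.

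**3. Offset b in SPADI points (D and s both assumed).**

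| D (days) | s = 0.5 | s = 1 | s = 2 | s = 3 |
|---|---|---|---|---|
| 0.5 | 0.25 | 0.5 | 1 | 1.5 |
| 1 | 0.5 | 1 | 2 | 3 |
| 2 | 1 | 2 | 4 | 6 |
| 3 | 1.5 | 3 | 6 | 9 |

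**4. A partial anchor for D.** If LOS fell only through fewer PPCs, D = (0.20 − 0.05) × extra days per PPC. Background says that PPCs lengthen stay but gives no number. Assuming 3 to 10 extra days, D = 0.15 × 3 = 0.45 to 0.15 × 10 = 1.5 days. With s from 0.5 to 3, b runs from 0.45 × 0.5 ≈ 0.2 to 1.5 × 3 = 4.5 points. By this route alone, a mean difference of one day needs 1/0.15 = 6.7 extra days per PPC. This is not a ceiling, since earlier ambulation could also shorten the stay.

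**5. Effect on a test at discharge.** Take 84 per arm, a two-sided normal test at 0.05 and no true shoulder effect. Then SE = SD × √(2/84), and the rejection rate is 1 − Φ(1.96 − b/SE) + Φ(−1.96 − b/SE). For SD 20 (assumed), SE = 3.09. With b = 4, b/SE = 1.30 and the rate is 25.4%.

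| b | SD 15 | SD 20 | SD 25 |
|---|---|---|---|
| 0.5 | 5.5% | 5.3% | 5.2% |
| 1 | 7.2% | 6.2% | 5.8% |
| 2 | 13.9% | 9.9% | 8.1% |
| 4 | 40.8% | 25.4% | 17.9% |
| 6 | 73.6% | 49.4% | 34.3% |

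If H1 holds and s is positive, the excess rejections point towards apparent harm from physiotherapy.

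**6. Effect on the ANOVA.** If all four time levels enter with complete data, b shifts the group difference averaged over levels by b/4 (1 point when b = 4). The group-by-time test sees the whole of b at one level.

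**7. What is outside the problem.** The 1- and 3-month assessments are dated from surgery, so D does not enter them. Muscle strength is not measured at discharge, and PPC is the separate primary outcome.

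**The case against.** **Size and direction.** Every input to the size is assumed, and at the low end the offset is trivial. The article does not say that pain or shoulder limitation eases daily in the first week; Background speaks only of chronic pain and long-term restriction. This stands. A reader might infer that the discharge contrast is certainly biased by a material amount, or that only equal discharge timing removes the bias. The documents support neither: the bias needs both a LOS difference and ongoing recovery, and flat recovery also gives zero.

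**Discharge as a time point.** Discharge marks the end of daily inpatient treatment and the start of the home programme, and condition on leaving hospital matters to patients. This stands for description. But nothing in the article limits the discharge values to that use.

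**Consequence.** One time point of secondary outcomes is affected, ROM is a subgroup measure, and under H1 the bias would not produce a false claim of benefit. This stands and limits the weight of the point. A reader might go further and conclude that H2 as a whole is compromised. That does not follow: muscle strength and the later contrasts are sound, and Data analysis neither names SPADI or pain nor says which time levels enter each ANOVA.

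**Unseen analysis plan.** It could specify how assessment time is handled, and LOS is recorded for everyone. It cannot, however, move a measurement whose timing is fixed here. Entering days to discharge as a covariate would adjust for something treatment may change.

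**Conclusion.** The point holds as a conditional weakness of one secondary time point. The plan measures SPADI, pain and ROM at an event whose timing H1 expects treatment to change, and it states no safeguard in the between-group comparison. If LOS differs and recovery is still under way, the discharge contrast, and any ANOVA group or group-by-time test that includes it, does not isolate the treatment effect. If H1 is true and patients are improving, the error works against physiotherapy.

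Its size cannot be computed from the article. Under the assumed inputs it runs from about 0.5 SPADI points or less, with the error rate hardly moved from 5%, to several points, where a test at discharge could reject far too often. A trial designed in the expectation of H1 should have shoulder comparisons that remain valid when H1 is true.

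**What to change.** State that between-group claims on SPADI, pain and ROM, including those under H2, rest on the 1-month and 3-month assessments, adjusted for the preoperative value. Leave discharge out of the tested levels. Report discharge values by group as status on leaving hospital, with the postoperative day of assessment. Do not adjust for days to discharge.

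This is a change of analysis wording and needs no new data. The cost is one tested secondary time point.

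If an in-hospital comparison is wanted, a single fixed postoperative day for both arms would remove the timing difference only if it is early enough that almost no patient has left. Allowing measurement on the day of discharge when that comes sooner would bring the problem back for early leavers. A fixed day is a change to the visit schedule, not just to wording.
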